## Abstract

**Purpose:**

Proximal hamstring tendinopathy (PHT) presents as localised lower buttock pain with tasks such as squatting and sitting. It is a condition that occurs at all ages and levels of sporting participation and can cause disability with sport, work, and activities of daily living.

This paper details a pilot trial protocol for investigating the effectiveness of individualised physiotherapy compared to extracorporeal shockwave therapy (ESWT) on pain and strength in people with PHT.

**Methods:**

The study is an assessor-blinded, pilot randomised controlled trial (RCT). One hundred participants with PHT will be recruited from the local community and sporting clubs. Participants will be randomised to receive six sessions of either individualised physiotherapy or ESWT, with both groups also receiving standardised education and advice.

Primary outcomes will be global rating of change on a 7-point Likert scale, and the Victorian Institute of Sport—Hamstring (VISA-H) scale, measured at 0, 4, 12, 26 and 52 weeks. Secondary outcomes will include sitting tolerance, the modified Physical Activity Level Scale, eccentric hamstring strength, modified Tampa scale for kinesiophobia, the Örebro Musculoskeletal Pain Screening Questionnaire Short Form (ÖMPSQ-SF), Numerical Pain Rating Scale (NPRS) for average and worst pain, participant adherence, the Pain Catastrophizing scale, satisfaction scores, and quality of life. Data will be analysed on an intention to treat basis, with between-group effects estimated using linear mixed models for continuous data and Mann Whitney U tests for ordinal data.

**Conclusions:**

This pilot RCT will compare individualised physiotherapy versus ESWT for PHT. The trial will determine feasibility and estimated treatment effects to inform a definitive trial in the future.

**Trial registration:**

The trial has been prospectively registered with the Australia & New Zealand Clinical Trials Registry (ACTRN12621000846820), registered 1 July 2021, https://www.anzctr.org.au/Trial/Registration/TrialReview.aspx?id=373085

**Supplementary Information:**

The online version contains supplementary material available at 10.1186/s40634-023-00615-x.

## Background

Proximal hamstring tendinopathy (PHT) affects active people, particularly those participating in running, lunging, or kicking sports. This condition was initially described in 1988 [1] as ‘hamstring syndrome’ and typically is associated with focal lower buttock pain, aggravated by prolonged sitting, running/walking, lunging and squatting [2–4].

Tendinopathy is attributed to acute and/or chronic overloading or unloading of the tendon. Tendon loading comprises of tensile and compressive components. Acute loading can result in reactive tendinopathy [5] that manifests as tendon swelling due to increased large proteoglycan content, but without collagen disruption. Chronic overloading can lead to ‘disrepair’ or ‘degenerative’ [5] tendinopathies, with collagen and tendon matrix disorganisation.

While the primary function of tendons appears to be to transmit tensile loads, compressive forces have been shown to be a contributor to adaptive changes of the tendon matrix and development of tendon pathology [6]. Compressive load in PHT generally occurs at the ischial tuberosity during activities involving deeper ranges of hip flexion, such as squatting, lunging, kicking and hamstring stretching, or with direct compression in sitting. Activities involving compressive loading are commonly provocative in PHT [3, 4]. Surgical [7] and imaging [8] studies show the location of tendinopathic change in PHT is adjacent to the ischial tuberosity insertion in PHT suggesting compression as a key factor in the development of this condition.

There is limited research on the diagnostic criteria for PHT and an absence of a diagnostic gold/reference standard suitable for robust studies on diagnostic accuracy. A study [9] on diagnostic accuracy using MRI as the reference standard investigated three different stretching tests. However, the conclusions of this research are limited because of the high prevalence of abnormal proximal hamstring findings in asymptomatic people [10].

Based on biological plausibility, there is general consensus on the importance of pain on tensile and/or compressive loading of the tendon (such as in muscle contraction, functional tasks, stretching or sitting [1, 3, 4, 11]), and pain location over the proximal tendon as clinical features indicative of PHT [12–16]. An additional potentially relevant clinical feature is a history of increased tendon load precipitating onset of symptoms [3, 11].

A number of treatment options have been proposed for PHT. Traditionally, conservative care has included load management, graded rehabilitation/exercise, selective use of oral non-steroidal anti-inflammatory drugs, and manual therapy techniques [3, 4]. Injection therapies such as platelet rich plasma, autologous blood injection and corticosteroid injection have also been investigated. There is an absence of high-quality research demonstrating effectiveness of these approaches in PHT [8, 17–21].

Extracorporeal shockwave therapy (ESWT) is a non-invasive and commonly used treatment that has demonstrated effectiveness in a variety of tendinopathies [22–26]. The mechanisms underpinning the effects of ESWT in tendinopathy are uncertain but reduced pain pressure threshold has been demonstrated in normal Achilles tendons [27, 28]. Changes in tendon collagen structure in normal animal tendons [27, 29] have also been demonstrated in response to ESWT. An RCT comparing ESWT to conservative care for PHT, [2] showed superior results on pain and function at 3-month follow-up, although trial limitations included the conservative program not reflecting successful protocols in other tendinopathy trials, [30] and being generic rather than individualised to participant presentation [31].

Recent narrative reviews and mechanistic papers support the use of individualised rehabilitation for PHT. Key recommendations include progressive strengthening exercises, graduated reintroduction of compressive loads, restoration of tendon energy storage and release capacity and return to normal activity [3, 11]. Progressive strengthening programs have demonstrated improvement in pain, disability and function in other lower limb tendinopathies [32–45] however this approach has not been evaluated for PHT particularly when individualised to the participant presentation; an approach common in other musculoskeletal research [46–48].

Given the shortcomings of the literature as described above, there is need for further evaluation on the effectiveness of individualised physiotherapy for people with clinical features indicative of PHT. The aim of this paper is to describe the design of a pilot RCT comparing the effectiveness of individualised physiotherapy (‘PHYSIOTHERAPY’) with ESWT (‘SHOCKWAVE’) on pain, strength and function for people with PHT. The objectives for this trial are to assess feasibility of recruitment and follow up of people with PHT for a future effectiveness trial, and to measure outcome domains (including for global rating of change, pain, function and sporting participation) in participants with PHT.

## Methods/design

### Study design

This trial will be an assessor-blinded, pilot RCT comparing two interventions: PHYSIOTHERAPY and SHOCKWAVE (Fig. 1).

**Fig. 1 Fig1:**
[figure not shown]
Study design

### Patient and public involvement

There was no formal involvement of participants in the study design however two of the researchers treat people with PHT providing indirect patient input into the development of the study protocols.

### Ethics and registration

Ethical approval has been received from the La Trobe University Human Ethics Committee (HEC21049). The trial has been prospectively registered with the Australia & New Zealand Clinical Trials Registry (ACTRN12621000846820).

### Setting

Treatment will be conducted at private physiotherapy practices throughout Victoria, Australia.

### Eligibility and screening

Participants will be sought via referrals from orthopaedic surgeons, physiotherapists, medical practitioners and through direct public advertising. Personal correspondence, group presentations, formal meetings and trial information sheets will be used to inform potential referrers. This will be supplemented with public advertising about the trial through social media and print media.

Participants with clinical features of PHT, aged from 18–65, will be recruited. Initial eligibility screening will occur via telephone. The clinical examination with the lead researcher will confirm eligibility and provide descriptive information on the baseline characteristics of participants. Participants will need to have clinical features indicative of PHT including: localised ischial tuberosity region pain, a history of increased tendon load precipitating onset of symptoms, and reproduction of pain on three or more loading/compressive tests (Figs. 2 and 3, Table 1). All tests have biological plausibility for providing high compressive ± tensile load to the tendon and have consensus in the literature as being beneficial in diagnosing PHT [3, 4, 11]. If eligibility is confirmed at clinical examination, the volunteer will be sent the study plain language statement and consent form that explains the study requirements, procedures, and time commitments.

**Fig. 2 Fig2:**
[figure not shown]
Single leg arabesque

**Fig. 3 Fig3:**
[figure not shown]
Single leg hamstring bridge

**Table 1 Tab1:** Eligibility criteria

**Inclusion Criteria**
* Initial Phone Screening*
1. Reports of relatively localised (defined as an area smaller than a tennis ball) ischial tuberosity region pain [3] of gradual onset and at least 3 months in duration
2. Willingness to participate in six sessions of intervention over a 12-week period
3. Age between 18 and 65 inclusive
4. Fluency in English sufficient to complete questionnaires and to enable understanding to the intervention
5. Agreeing to refrain from other interventions for the treatment period of the trial, aside from consultation with medical practitioners, and medication
* Clinical examination screening*
6. A history of increased tendon load precipitating the onset of symptoms determined based on clinical interview
7. Reproduction of ischial tuberosity region pain with three or more of the following loading/compressive tests:
• Single-leg arabesque (Fig. 2)
• Supine single leg bridge with heel on standardised height platform (bent knee) (Fig. 3)
• Self-reported PHT symptoms with prolonged sitting < 30 min
• Modified bent-knee hamstring stretch test [9]
**Exclusion Criteria**
* Initial Phone Screening*
1. Previous surgery to the hamstring complex, as we wish to study treatment effects independent to the effects of surgical procedures
2. Previous injection to the hamstring tendon within the previous 6 weeks, as we wish to study treatment effects independent to the effects of injections
3. Treatment with ESWT for PHT in the last 3 months, [26] as this may influence progress during the trial
4. Contraindications to receiving ESWT [49]
5. Current pregnancy, or recent childbirth (within 6 months) as this could impair ability to undertake testing and intervention
6. Diagnosis with autoimmune disease as these conditions may have a negative impact on tendon
7. Already received more than two sessions of physiotherapy with any of the trial physiotherapists prior to enrolment, as these therapists are likely to use components of the trial treatment protocol on their clinical caseload
8. An active compensation claim for the injury, as this may influence the response to treatment [50]
9. Planned absence for a period of > 2 weeks during the treatment period (such as extended holiday)
* Clinical examination screening*
10. Pain that is predominantly due to lumbar dysfunction including lumbar spine radiculopathy, [51] or lumbar spine somatic referral (Additional file 1)
11. Pain that is reasoned from clinical examination to be predominantly due to other structures or conditions, including sciatic nerve entrapment, ischiofemoral impingement, hip joint, local sciatic nerve irritation, and adductor magnus tendinopathy (Additional file 1)

### Randomisation and allocation

Following provision of written consent, participants will be randomised into one of two intervention groups: PHYSIOTHERAPY or SHOCKWAVE. A researcher located remotely at La Trobe University who will have no contact with trial participants will prepare a randomisation schedule ahead of time. The randomisation sequence will be generated electronically by an online randomisation program that incorporates random block sizes. Randomisation will be stratified for age (< 50 years of age vs >  = 50 years of age), as systemic factors associated with menopause may influence response to some components of treatment [52–55]. Concealed allocation of participants in accordance with the randomisation schedule will be undertaken by the same researcher at La Trobe University who will be the only person with access to the allocation spreadsheet during the trial. To enrol a participant, the primary researcher (AR) will email the consenting participant’s name and date of birth to the La Trobe University researcher, who will enter the patient into the trial and notify the primary researcher of the treatment group allocation. These details will be entered into the allocation spreadsheet and the next intervention allocation and participant identification number will be emailed to the primary researcher who will contact the treating physiotherapist who will arrange the initial appointment.

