#### Participating physiotherapists and treatment fidelity

Physiotherapists from private practices in Victoria will provide treatment for both groups. To be eligible, the physiotherapists will need to have at least 2 years of clinical experience. Physiotherapists will then participate in a small group, 4-h training session provided by the lead researcher (AR). The program will include review of previously provided material, and simulation of explanations and treatments to be used in the trial.

Treating physiotherapists will be provided with a treatment manual detailing treatment algorithms, protocols and participant information sheets. Treatment methods will be clearly defined and standardised via a detailed session-by-session electronic clinical notes template containing a series of decision-making algorithms. The algorithms and clinical notes will ensure that essential elements of the treatment program are consistently applied by all physiotherapists across all participants, while still allowing some opportunity for the treatment to be tailored to individual participant presentation. The template will require treating physiotherapists to provide physical assessment findings, justification and rationale for clinical decision making, detail of treatment provision/prescription and response to treatment. Physiotherapists will be required to complete electronic clinical notes for each session which detail assessment findings, treatment provided, clinical decision-making justification and any adverse events from shockwave treatment or the exercise program.

A quarterly face-to-face meeting will be undertaken for 60 min involving all treating physiotherapists for the duration of the trial to review de-identified cases in the context of the treatment protocol. Evaluation of treatment fidelity and adherence by the physiotherapists for specific rehabilitation techniques will be achieved by checking the physiotherapist’s clinical notes for each participant after the second and fourth sessions of the program.

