### Adverse events

Adverse events occurring during the treatment period will be recorded by the physiotherapist in the standardised clinical notes of each participant. Any serious adverse events will be immediately reported to the lead researcher, who will investigate and organise medical care (if required) and report to the ethics committee. The lead researcher will review the clinical notes and questionnaires after 4 weeks of treatment to screen for any unreported adverse effects of treatment. Participants will be provided opportunity on follow-up questionnaires to report any unpleasant, adverse, or harmful effects they ascribe to the treatment.

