### Blinding

It is not feasible to blind participants or treating physiotherapists due to the nature of the interventions. However, treating practitioners and researchers will inform participants that both treatment approaches have a realistic chance of providing success and that neither has been shown to be superior in previous trials. Physiotherapists will be advised to treat both groups of participants with the same level of expectation and enthusiasm. Strength outcomes will be measured by a blinded assessor. Data analysis will be performed using data without identifying group labels, to ensure blinded analysis.

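### Every allocation is emailed to the researcher who confirms eligibility and requests enrolment, so past assignments are known and the next one can be guessed better than chance

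*Protocol article*

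**What the plan says.** All references are to the Protocol article.

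- **Randomisation and allocation.** A remote researcher without participant contact prepares the schedule, using random block sizes and stratifying by age (under 50, 50 and over). The same person makes the allocations and is the one "who will be the only person with access to the allocation spreadsheet during the trial". Randomisation follows written consent. The primary researcher emails the enrolment request, and then "the next intervention allocation and participant identification number will be emailed to the primary researcher who will contact the treating physiotherapist".
- **Eligibility and screening.** "The clinical examination with the lead researcher will confirm eligibility". The consent form is sent after that.
- **Table 1.** Some criteria call for judgement. Inclusion 6 reads "A history of increased tendon load precipitating the onset of symptoms determined based on clinical interview". Exclusion 11 covers "Pain that is reasoned from clinical examination to be predominantly due to other structures or conditions" and refers to Additional file 1.
- **Participating physiotherapists and treatment fidelity.** Physiotherapists attend a "4-h training session provided by the lead researcher". The initials given there match those of the primary researcher in the randomisation section, so the two roles are one person. Clinical notes are checked after sessions two and four, by someone not named.
- **Adverse events.** "The lead researcher will review the clinical notes and questionnaires after 4 weeks of treatment".
- **Blinding.** "It is not feasible to blind participants or treating physiotherapists due to the nature of the interventions". Blinding covers the strength assessor and the handling and analysis of the data.

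**The concern.** Keeping the list remote stops anyone reading ahead. It does not stop prediction when the list's past entries reach the recruiter one at a time. In a blocked scheme the arm that is behind within a stratum is more likely to come next, and the recruiter knows each candidate's stratum from their age. Random block sizes hide where a block ends but leave this tendency in place.

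The recruiter has two points of discretion: the judgement-based part of eligibility, and when the enrolment email goes out. The Discussion states a hypothesis favouring PHYSIOTHERAPY from 12 weeks on, and both primary outcomes are self-reported by unblinded participants. Adjusting for baseline VISA-H would absorb some selection, but not selection on unmeasured prognosis such as a doubtful diagnosis. The global rating of change has no baseline value. The effect estimates are intended to inform a definitive trial, which might also copy the procedure.

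**Working it through.** **The plan's own figure.** The article gives no figure for predictability. Its sample size reproduces: a two-sided 5% t-test with 80% power at a standardised difference of 0.6 needs 44.6, so 45, per arm, and 90 / 0.9 = 100. This point does not affect it; the 45 per arm is reused below.

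**Inputs.** From the article: 100 participants, two age strata, random permuted blocks, all past arms known to the recruiter. Assumed: 1:1 allocation, the block sizes, and strata of 50 and 50 (70 and 30 gives the same results).

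**Guessing rule.** Choose the arm that is behind in the stratum; toss a coin if tied.

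*Hand check, fixed block of 4.* The chance of a correct guess at positions 1 to 4 is 1/2, 2/3, (2/3)(1/2) + (1/3)(1) = 2/3, and 1, which sum to 2.833. A stratum of 50 holds 12 full blocks plus two positions: (12 × 2.833 + 0.5 + 0.667) / 50 = 70.3%. Simulation gives 70.4%.

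*Random blocks, simulated.* The last column assumes one unseen same-stratum enrolment between the guess and the allocation.

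| Assumed block sizes | Correct, just before allocation | Known with certainty | Correct, one enrolment in between |
|---|---|---|---|
| 2, 4 | 72% | 11% | 55% |
| 2, 4, 6 | 70% | 4% | 58% |
| 4, 6 | 69% | 6% | 59% |
| 4, 6, 8 | 68% | 2% | 60% |

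Blocks of 6, 8 and 10 give 66% just before allocation. Simple randomisation gives 50%. An optimal guesser who knows the set of block sizes scores the same as the simple rule, so that knowledge is not needed. The certainty column does assume it. For comparison, a fixed block of 4 leaves 32% of assignments certain: random sizes remove most of the certainty but little of the better-than-chance guessing.

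**Illustration of bias.** Suppose entrants guessed for PHYSIOTHERAPY have expected outcomes η SD higher, and those guessed for SHOCKWAVE η SD lower. With accuracy p, each arm's mean shifts by η(2p − 1) in opposite directions, so the bias is 2η(2p − 1).

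- p = 0.70: η = 0.10 gives 2 × 0.10 × 0.40 = 0.08 SD; η = 0.25 gives 0.20 SD.
- p = 0.60: η = 0.10 gives 2 × 0.10 × 0.20 = 0.04 SD; η = 0.25 gives 0.10 SD.

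For a t-test with 45 per arm (88 degrees of freedom, non-centrality bias × √(45/2)) and no true effect, the rejection rate is 6.6% at 0.08 SD, 15.5% at 0.20 SD and 5.4% at 0.04 SD. No value of η comes from the article.

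**What rerouting achieves.** July 2021 to early 2023 is about 18-20 months, so 100/20 to 100/18 = 5.0-5.6 enrolments a month, or about 2.5-2.8 per stratum if evenly split. If the lead researcher first learns each arm at the 4-week review, the last 2-3 assignments per stratum are hidden and accuracy falls to about 50-57%. Sessions fall at weeks 0, 1, 2, 3, 6 and 12, so the note checks after sessions two and four come at about weeks 1 and 3, before that review. If the lead researcher did those checks, much of the gain would be lost.

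**The case against.** The strongest reply is about timing. Eligibility is settled at the examination, the consent form goes out afterwards, and randomisation follows written consent. A guess made when eligibility is judged is weakened by anyone enrolled in the meantime: one same-stratum enrolment cuts it to about 55-60%. This stands and limits the eligibility route. It does not touch the second route, since the same person decides when the enrolment email is sent, although nothing in the article suggests that timing is used in this way.

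Other points that stand:

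- Eligibility is not free judgement. Inclusion 7 is a count of positive tests, and exclusions 10 and 11 refer to Additional file 1, which is not shown and may tighten them.
- The assumed shift of 0.1-0.25 SD is a contrast of 0.2-0.5 SD between the two guess groups at every enrolment, set beside a detectable difference of 0.6. The upper error rates describe sustained, systematic selection, and they ignore baseline adjustment.
- This is a pilot with feasibility objectives, and remote custody, random blocks and release only after consent are all in place.

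A reader might also infer that the upcoming assignment is disclosed in advance, making prediction perfect. The article does not support that. The allocation described as next is sent with the identification number once the consenting participant's details are entered, so it most naturally means the next line of the schedule, given to that participant. Nor is it a finding that the article does not say when the treating physiotherapist is chosen; a condensed article may leave that out.

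What the objection does not remove is the routing itself, which the article states outright.

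**Conclusion.** The concern holds as an avoidable risk of selection bias. One person confirms eligibility, requests enrolment and receives every allocation in an open, blocked trial. Guessing accuracy is about 68-72% when the enrolment email is sent and about 55-60% after one intervening same-stratum enrolment. Both ranges rest on assumed block sizes, but every set tried stays well above 50% just before allocation.

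A reader might infer that the trial's 5% test truly runs at 6.6-15.5%, or that the list is exposed. Neither follows. The error rates need a selection shift that has no source in the article, and they serve only to show the scale. The list itself is properly held, and nothing suggests that allocations were subverted.

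**What to change.** 1. In Randomisation and allocation, have the enrolment email declare eligibility final and name the treating physiotherapist. The remote researcher then sends that participant's allocation and identification number directly to that physiotherapist, not to the primary researcher. List, random blocks and strata stay as they are.
2. While recruitment is open, have the note checks after sessions two and four done by an existing team member who does not judge eligibility. The lead researcher's 4-week review then becomes the earliest routine point at which that person learns the arm. Rerouting the email without this step would not be enough.
3. For clarity only, refer to that participant's allocation instead of the next one.
4. Add to the limitations in the Discussion that, for participants already enrolled, the person confirming eligibility knew previous allocations. Protocol version 7 is dated 7 March 2023 and recruitment was expected to end in early 2023, so this may be the main action left for this trial. Items 1 and 2 serve any remaining enrolment and the definitive trial.

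The cost is a different addressee for an email already being sent, a reassigned check and a few sentences of text, with no extra participants or staff. The downside is that the lead researcher learns each arm later and loses some control over coordination. Individual arms may still become known earlier through queries or serious adverse event reports.
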